### Setting

Patients receiving a permanent end-colostomy in an elective setting will be recruited from the following centers:

Canisius Wilhelmina Hospital, Nijmegen; Radboud University Nijmegen Medical Centre, Nijmegen; Rijnstate Hospital, Arnhem; Maxima Medisch Centrum, Veldhoven; St Antonius Hospital, Nieuwegein; Catharina Hospital, Eindhoven; AMC Amsterdam, Amsterdam; OLVG, Amsterdam; University Medical Center Utrecht; Utrecht; Isala Clinics, Zwolle; Erasmus Medical Center, Rotterdam; Slingeland Hospital, Doetinchem; Medisch Spectrum Twente, Enschede; Albert Schweitzer Hospital, Dordrecht, The Netherlands.

The total trial period is estimated to be 7 years; the recruitment period will be 2 years, followed by a 5-year follow-up period.

### Inclusion criteria

• Patients undergoing formation of a permanent end-colostomy in an elective setting regardless of benign or malignant disease.

• Age between 18 and 85 years.

• Signed informed consent.

• Able to understand the study questionnaires.

### Exclusion criteria

• Expected survival <12 months.

• Stoma formation in an emergency setting.

• Formation of an ileostomy.

• Correction of a previous constructed colostomy.

• Previous surgery at the colostomy site.

### Ethical considerations

This trial is conducted in accordance with the Declaration of Helsinki and ‘Good Clinical Practice Guidelines’. It is approved by the Medical Ethics Committee of Nijmegen (CMO-ABR 22695). All local Medical Ethics Committees approved the final protocol.

Patients willing to participate in the trial will be provided with a patient information sheet and a reconsideration period. They will be included after written informed consent is obtained.

The PREVENT-trial is registered at:

http://www.trialregister.nl/trialreg/admin/rctview.asp?TC=2018

### Reporting

All results will be reported according to the CONSORT 2010 statement.

### Randomization

Randomization will be performed by telephone using an interactive voice response system. Patients are randomized by computer, treatment will be stratified and blocked by center to ensure each center has similar numbers of patients allocated to one of the two treatment groups.

### Safety and quality control

The trial coordinator will monitor all centers in order to identify non-compliance to protocol and serious adverse events (SAEs). SAEs are defined as any event leading to major complications and/or prolonged hospital stay due to the placement of the mesh. SAEs will be reported to the Data Safety Monitoring Board and to the accredited Medical Ethical Board (METC).

A Data Safety Monitoring Board will perform interim safety analyses and make recommendations regarding the conduct of the study to the accredited METC and the trial committee. When the mesh related complication rate is higher than 15%, the trial will be terminated.

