## Abstract

**Background:**

Parastomal hernia is a common complication of a colostomy. Ultimately, one-third of patients with a parastomal hernia will need surgical correction due to frequent leakage or life-threatening bowel obstruction or strangulation. However, treatment remains a challenge resulting in high recurrence rates. Two single center trials demonstrated that the frequency of parastomal hernias decreases by prophylactic placement of a mesh around the stoma at the time of formation. Unfortunately, both studies were small-sized, single-center studies and with these small numbers less common complications could be missed which were the reasons to initiate a prospective randomized multicenter trial to determine if a retromuscular, preperitoneal mesh at the stoma site prevents parastomal hernia and does not cause unacceptable complications.

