## Methods

### Study objectives

The aim of this single-blind, multicenter, randomized controlled trial is to determine if parastomal herniation is prevented by the prophylactic placement during open surgery of a polypropylene mesh around a colostomy. Patients are blinded and are not aware if mesh placement did occur. Most surgeons will see their own patients postoperatively in the outpatient clinic so double blinding was not feasible and could not be guaranteed. Patients are randomized into two groups. In one group a preperitoneal, retromuscular positioned polypropylene mesh is placed around the stoma. In the control group a conventional stoma is created.

It is hypothesized that mesh placement will reduce the incidence of parastomal hernia of 30% down to 10%.

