#### Secondary endpoints

Secondary endpoints are perioperative morbidity, including stomal necrosis, stenosis, parastomal, or laparotomy wound infections. Mortality, pain, quality of life, and cost-effectiveness are other secondary endpoints that will be analyzed.

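### The SAE definition requires attribution to the mesh, so SAE counts and the SAE reports to the DSMB and ethics board have no control-arm rate

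*Protocol article*

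**What the plan says.** Protocol article, Safety and quality control: "SAEs are defined as any event leading to major complications and/or prolonged hospital stay due to the placement of the mesh". The same section sends SAEs to the DSMB and the accredited ethics board, and says that the DSMB performs interim safety analyses. It adds a termination rule: "When the mesh related complication rate is higher than 15%, the trial will be terminated".

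Study objectives: "In the control group a conventional stoma is created". The trial is single-blind: patients do not know their arm, and because most surgeons see their own patients after the operation, double blinding was judged not feasible.

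Abstract, Background: the trial is to establish whether the mesh "prevents parastomal hernia and does not cause unacceptable complications".

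Secondary endpoints: "Secondary endpoints are perioperative morbidity, including stomal necrosis, stenosis, parastomal, or laparotomy wound infections". Mortality is also listed. Neither is tied to the mesh.

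**The concern.** An SAE is normally identified by how serious the event is, and its cause is judged afterwards. Here the causal judgement decides whether the event is an SAE at all. This has three consequences.

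- A patient who received no mesh cannot have an SAE, however serious the event.
- In the mesh arm, the count depends on a judgement of relatedness. The article describes no blinded assessment of it.
- An event judged unrelated in either arm, such as a reoperation or readmission, need not reach the DSMB or ethics board by the SAE route.

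Safety is part of the reason for the trial. The Background section faults the earlier trials because their size could hide less common complications and because their reporting was not uniform. A randomised comparison can show an excess of harm made up of events that nobody would individually blame on the mesh. A one-armed SAE stream that depends on attribution cannot.

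**Working it through.** The plan gives no figure for this point, so there is none to reproduce. The check is a reading of the sections against each other, followed by an illustration of size.

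**Step 1. Who can have an SAE?** The definition needs an event caused by placing a mesh. The control arm gets none, so the possible SAE count there is 0 for every patient treated as allocated. There is one small exception. Under Data collection, patients not treated as allocated stay in the trial by intention to treat, so a control patient who was given a mesh could have an SAE.

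**Step 2. Does another reading of the sentence rescue it?** The causal phrase could be taken to qualify only the prolonged stay. Major complications would then count in both arms, but a prolonged stay would still count in one arm only. The definition stays asymmetric. The termination rule in the same section, also framed as mesh-related, favours the reading in Step 1.

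**Step 3. What do other sections capture in both arms?**

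| Section | Content | Tied to mesh? |
|---|---|---|
| Safety and quality control | SAEs, reported to DSMB and ethics board | Yes |
| Secondary endpoints | Perioperative morbidity, mortality | No |
| Follow-up and definitions of complications | Infection (CDC criteria), dehiscence, necrosis, stenosis, leakage | No |
| Cost analysis | Volumes of care per patient, costed per arm | No |

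Reoperation and readmission are not named in the second or third row, and the morbidity endpoint is described as perioperative while follow-up runs to 5 years.

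**Step 4. Illustration.** Inputs: 150 patients in total (Patient sample size); equal allocation is assumed, so 150 / 2 = 75 per arm. The event rates and the attributed share below are assumptions, since the article gives none. Let p0 and p1 be the true proportions of patients with a serious event in the control and mesh arms, and a the share of mesh-arm events attributed to the mesh.

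- Reported SAEs, mesh arm: 75 × p1 × a
- Reported SAEs, control arm: 0
- True excess: 75 × (p1 − p0)

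| p0 | p1 | True events, control | True events, mesh | True excess | Reported (mesh vs control) at a = 0 | a = 0.5 | a = 1 |
|---|---|---|---|---|---|---|---|
| 10% | 10% | 7.5 | 7.5 | 0 | 0 vs 0 | 3.75 vs 0 | 7.5 vs 0 |
| 30% | 30% | 22.5 | 22.5 | 0 | 0 vs 0 | 11.25 vs 0 | 22.5 vs 0 |
| 10% | 20% | 7.5 | 15 | 7.5 | 0 vs 0 | 7.5 vs 0 | 15 vs 0 |

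The reported difference equals the true excess only when a = (p1 − p0) / p1, which is 0 in the first two rows and 0.5 in the third. For any other value of a, the SAE line overstates or understates the harm, and the SAE data cannot show which.

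**The case against.** The strongest reply is that the safety question does not rest on SAE counts. No section makes them an endpoint. Perioperative morbidity and mortality are compared between randomised arms, complications have arm-neutral definitions, and care use is recorded in both arms. Under the equal-rate rows above, stoma and wound events of the listed kinds would appear in that comparison at 7.5 vs 7.5 or 22.5 vs 22.5. This stands. A reader might infer from the definition that the trial cannot compare serious harm between arms at all. The article does not support that.

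Two other inferences also go too far. The first is that the DSMB sees only one-armed data: its interim safety analyses are not said to be limited to SAEs. The second is that the unblinded surgeon decides relatedness: the article does not say who does. It gives the trial coordinator the task of identifying SAEs and provides for independent monitoring visits. Exposure to unblinded judgement is likely, because most surgeons know the allocation, but it is not stated.

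The reply does not cover the SAE stream itself. SAEs are the only data that the article says are reported to the DSMB and ethics board, and that stream has no control rate. Nor do the listed endpoints clearly reach late reoperation or readmission.

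**Conclusion.** The definition is wrong as written, and it should be fixed. It makes SAE counts, and the SAE reports to the DSMB and ethics board, incomparable between arms. Serious events that are judged unrelated, or that lie outside the listed endpoints, may not be reported by this route. This fits poorly with the aim of showing that the mesh "does not cause unacceptable complications".

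The structural result, a control count of zero apart from any control patient given a mesh, follows from the text alone. Its size in patients does not. The figure of 7.5 to 22.5 uncounted control patients rests on assumed rates of 10% to 30% and equal allocation.

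The point falls short of a must-fix because the primary endpoint and the comparative harm endpoints are unaffected.

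**What to change.** Define an SAE by seriousness alone, in the same way in both arms and whatever the presumed cause. Record relation to the mesh as a separate CRF field, so that the mesh-related subset remains available. Report SAEs by arm to the DSMB and in the final report, both overall and for the mesh-related subset. No treatment or clinical rule changes.

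The cost is a protocol and CRF amendment and a larger number of SAE reports. The Trial status section expects the planned number of patients within months, so a new definition alone would cover mainly later events. Earlier serious events in both arms would have to be identified retrospectively across the 14 hospitals. The existing CRFs are the natural source, since complications are already recorded at follow-up and copies of the forms go to the coordinating center.

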### Preoperative work-up

In an outpatient setting all participants receive information and guidance by a stomal therapy nurse. Stoma site marking is performed by a stomal therapy nurse prior to surgery. Colonic lavage will be performed if necessary. In both groups preoperative antibiotic prophylaxis will be given according to the local agreements.

### Surgical techniques

A light-weight monofilament polypropylene mesh, Parietene Light™ (Covidien®) is the mesh of choice for this study. This mesh is chosen because there is level 2b evidence that shrinkage of the mesh, postoperative foreign body sensation, and pain are less in comparison with traditional polypropylene mesh [15,16].

According to the technique of Jänes and Israëlsson, the intended bowel for the colostomy is closed with a stapling device, thus minimizing the chance of contamination. The trephine is created by excision of the skin-oval at the preoperatively marked ostomy site. No subcutaneous tissue is excised. After exposing the anterior rectus sheath, a cross-shaped incision is made in the fascia. The rectus abdominus muscle is split in the direction of the fibers. In the mesh group a retromuscular space is created and dissected to the lateral border via the median laparotomy. The posterior fascia/peritoneum is left undisturbed. A 10×10 cm Parietene Light™ mesh, with a cross-shaped incision in the center of the prosthesis to allow passage of the colon loop, is placed on the posterior rectus sheath (Figure 1).

**Figure 1 F1:**
[figure not shown]
Preparing the central hole for the bowel to pass through, no central portion is cut away.

The lateral corners of the mesh are fixed with two absorbable monofilament sutures. Then the posterior fascia is opened over the trephine in the mesh and the bowel is gradually passed through. Closing the midline incision, the running suture includes the medial border of the mesh and the peritoneum, thus preventing contact between the mesh and the viscera (Figure 2). The stoma has to protrude 1 to 2 cm above the skin and is fixed with resorbable sutures to the skin [13].

**Figure 2 F2:**
[figure not shown]
**Cross-section through the abdominal wall.** The mesh is placed in the retromuscular plane on the posterior rectus sheath/peritoneum. The bowel is passed through the pre-shaped hole in the mesh and the rectus muscle. With the closure of the abdominal wall the mesh and the peritoneum are included in the running suture.

This technique is described in detail in the study protocol to ensure standardized mesh placement. It is available in text and on video on our website: http://www.preventtrial.nl.

### Follow-up and definitions of complications

Outpatient follow-up is scheduled at 3 weeks, 3 months, 1, 2 and 5 years postoperatively. Postoperative complications, such as peristomal infections, degree of stomal ingrowth, and leakage are recorded.

Parastomal hernia is defined as any detectable bulge in the vicinity of the ostomy with the patient erect, supine, and performing the Valsalva maneuver. Prolapse is scored if significant prolabation of bowel occurred causing the stoma to increase in length without peri-stomal bulging. Wound infection is defined in deep, superficial, or peristomal infections using the C.D.C criteria for surgical site infection [17].

Stomal dehiscence is defined as separation of the bowel mucosa from the skin, measured in millimeters. Stomal necrosis is defined as ischemia of the mucosal tissue. Stenosis is defined as narrowing of the stomal trephine leading to obstruction. Leakage is present if stomal material has to be replaced more than once every 2 days.

If there is a clinical or physical suspicion of a hernia a CT scan will be performed in a supine position with use of the Valsalva maneuver.

Quality of life and postoperative pain is determined using validated health scores preoperatively and during all moments of follow-up after the index operation.

### Health status scores

The SF-36 is a validated multi-purpose, short-form health survey. It yields an eight-scale profile of functional health and wellbeing scores as well as physical and mental health summary measures and a preference-based health utility index [18,19]. Completed preoperatively, 1 year, and 5 years after index operation.

Questionnaire of von Korff for Grading the Severity of Chronic Pain [20]. Three months and 1 year after the index operation.

EuroQoL-5D is an instrument which calculates an index which gives a societal-based quantification of the patients health status combined with a visual analogue scale [21]. This so-called health-related quality of life (HRQoL) instrument will be completed during every moment of follow-up. This index gives a societal-based global quantification of the patient’s health status.

### Cost analysis

The cost analysis exists of two main parts. First, on patient level, volumes of care will be measured prospectively using case record forms. Per arm (intervention and control) full cost-prices will be determined using activity based costing. Productivity losses for patients (sick leave) will be estimated by using the case record forms (CRFs). The friction cost-method will be applied following the Dutch guidelines [22].

The second part of the cost analysis consists of determining the cost prices for each volume of consumption in order to use these for multiplying the volumes registered for each participating patient. The Dutch guidelines for cost analyses will be used. For units of care/resources where no guideline or standard prices are available real cost prices will be determined.

### Data collection

All data will be collected in personal CRFs, which will be stored in the patient’s own hospital. Copies of the completed forms will be sent to our coordinating center (Canisius-Wilhelmina Hospital, Nijmegen). All data will be stored in a double-entry database (SAS). Independent monitoring visits will be performed throughout the entire duration of the trial. When patients are not treated according to their allocation, for any reason, they will stay in the trial following the Intention-to-Treat-principle.

### Trial status

The PREVENT-trial is currently open for recruitment. We expect to reach our powered number of included patients in the coming months.

## Abbreviations

CRF: Case record form; PSH: Parastomal hernia; RCT: Randomized Controlled trial.
